## INTRODUCTION AND RATIONALE

Since the introduction of digital pathology, the number of studies on artificial intelligence (AI) within the field of pathology have increased rapidly. These techniques have great potential to improve diagnostics by improving accuracy, reproducibility and speed. Algorithms have been created for tumor detection, tumor grading, recognizing tumor subtypes, evaluating biomarkers and more. Several of these algorithms have shown to be comparable, or even superior to pathologists. Worldwide, a shortage of pathologists exists. Combined with an increasing workload, this means that AI has great potential to alleviate the workload for pathologists.

However, AI has hardly been implemented in daily pathology practice. This is mainly because most of the datasets on which the existing algorithms were trained are considered not representative of daily clinical practice data, which are subject to many more sources of variation. However, AI keeps evolving and many of the above mentioned problems may have been overcome by the first FDA- and IVDR-approved algorithms, which are currently being released to the market. Lastly, there is a lack of prospective studies that pave the way for clinical implementation. As with any innovation in medicine these studies are required to address the true additional value of AI in pathology.

We use an IVDR-approved algorithm for detecting lymph node metastases in breast cancer (BCa) patients. Here, the task of the pathologist is both labor-intensive and costly, due to performed immunohistochemistry (IHC) stainings in case no tumor cells are morphologically observed. However, these stainings are expensive and their costs sometimes even exceed reimbursement for the entire resection specimen. This raises the question whether artificial intelligence may be of added value to morphologically detect cancer cells without the need for IHC-use. Thereby the amount of performed stainings may be reduced, which may keep health care costs sustainable, while potentially decreasing the workload of pathologists as well.

As breast cancer is the most common (non-skin) malignancy women, implementation of AI-assistance may have a great impact on diagnostic processes.

This study therefore aims to investigate the added value of AI-assistance for pathologists (augmented intelligence) in the identification of lymph node metastases in breast cancer patients.

## **1. OBJECTIVES**

### **Primary Objective**

To evaluate the added value of AI-assistance in detection of lymph node metastases in breast cancer in daily pathology practice, with regard to the number of spent resources (number of immunohistochemistry stains (IHC)), while maintaining diagnostic safety standards (by means of pathologist's supervision and staining in all negative cases).

### **Secondary Objective(s)**

- To evaluate the added value of AI-assistance with regard to workflow improvements (time and number of IHC-stains and costs)
- To evaluate pathologists performance (sensitivity and negative predictive value) in both trial-arms, and AI user-experience in the intervention arm.
- To evaluate AI-performance in both arms (standalone AI-performance in the intervention arm, retrospective standalone AI-performance in the control arm, and combined overall standalone AI-performance).

## **2. STUDY DESIGN**

The study will be a pragmatic diagnostic intervention trial, envisioned to start in April 2022 and end early 2023. The study settings are as follows:

All sentinel lymph node (SN) specimens of patients with breast cancer being assessed in the UMC Utrecht (these patients may be treated either in the UMC Utrecht or the Alexander Monro hospital) will be included sequentially.

### **General group assignment**

SN-specimens of breast cancer patients will be assigned to be assessed by a pathologist with or without AI-assistance in a pragmatic bi-weekly sequential design. This is deemed feasible as case-mix variation and time trends have not been observed previously, and as this is highly unlikely to occur within the envisioned inclusion-period of approximately six-nine months. Furthermore, specialized breast-pathologists within the UMCU work according to (bi)weekly schedules. Therefore using AI every two weeks, as opposed to switching by day, ensures that all breast pathologists are equally distributed between groups. Lastly, it would be unworkable to switch from AI-assistance to no AI-assistance on a case to case basis.

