### 6.1 Primary study parameter(s)

As the primary outcome measure is dichotomous, a simple Chi-squared test will be used to test for differences in the proportion of IHC-use in both arms. Furthermore, relative risks (of IHC-use) will be calculated.

For baseline comparisons between both arms, we will use the appropriate measures (parametric or non-parametric) for categorical (Chi-squared test/Fisher's exact) and continuous parameters (T-test, Mann-Whitney U test).

Although we do not expect differences in patient- and tumor characteristics between both groups, we will adjust for them if they are observed. We do not plan to perform the often used logistic regression model, but we will explore alternative models like Poisson regression with robust standard errors or log-binomial regression, as these will provide adjusted relative risks instead of odds ratio's provided by logistic regression.

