### Primary endpoint analysis

For the analysis of the primary endpoint, the proportions of IHC-use in all cases of detected SN-metastases were compared, and adjusted risks were calculated using a log-binomial regression model (1-6), with starting values provided by the simple approach suggested by Schwendinger *et al* (7, 8) and 95% confidence intervals (CI) calculated by bootstrapping (n=1,000) (1).

Potential confounders were identified a-priori during discussions with all participating pathologists. Two factors may play a role here. First how diligently a pathologist looks at the HE-section could potentially be influenced by tumor characteristics on biopsy. However, all participating pathologists stated that they virtually always look at an SN without prior looking at any of the tumor characteristics on biopsy. In this light, it is also important to mention that the SN-specimen is always assessed a day before the resection specimen of the tumor itself. Hence, many (if not all) tumor characteristics (either derived from the biopsy or the resection specimen) are unknown to the pathologist who assesses the SN-specimen. Second, some tumor characteristics may influence the visibility of metastasized cells. Two of these potential confounding factors were identified. First, the size of metastases (i.e. macro-metastases ( $\geq 2\text{mm}$ ), micro-metastases ( $< 2\text{mm}$ ) or ITC) influences their visibility to a pathologist (either with or without AI-assistance), and consequently influences the use of IHC. The same holds true for histologic subtype, as for example lobular cancer cells are known to be more difficult to identify on the HE-section.

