|---------------------------------------------------|------|--------------------------------------------------------------------------------------------------------------------------------------------------------------------------------------------------------------------------------------------------------------------------------------------------------------------------------------------------------------------------------------------------------------------------------|----------------|--|----------------------------------------------------------------------------------------------|
|                                                   |      | factors for stratification. To reduce predictability of a random sequence, details of any planned restriction (for example, blocking) should be provided in a separate document that is unavailable to those who enroll participants or assign interventions                                                                                                                                                                   |                |  | pragmatically every two weeks, which we explain in the Abstract and Methods section as well. |
| Allocation concealment mechanism                  | 16b  | Mechanism of implementing the allocation sequence (for example, central telephone; sequentially numbered, opaque, sealed envelopes), describing any steps to conceal the sequence until interventions are assigned                                                                                                                                                                                                             |                |  | See above, pragmatic, there was no allocation concealment.                                   |
| Implementation                                    | 16c  | Who will generate the allocation sequence, who will enroll participants, and who will assign participants to interventions                                                                                                                                                                                                                                                                                                     |                |  | See above, this was not applicable.                                                          |

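### Fixed two-week alternation does not guarantee that pathologists are balanced between arms, and no planned analysis takes reader or period into account

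*Combined protocol and SAP*

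**What the plan says.** Protocol section 2 (General group assignment) describes a "pragmatic bi-weekly sequential design". The premise offered for reader balance is that "specialized breast-pathologists within the UMCU work according to (bi)weekly schedules", and the conclusion drawn is: "Therefore using AI every two weeks, as opposed to switching by day, ensures that all breast pathologists are equally distributed between groups". The SPIRIT-AI checklist confirms allocation "pragmatically every two weeks, which we explain in the Abstract and Methods section as well", and on concealment states: "See above, pragmatic, there was no allocation concealment". It also records that there was no blinding.

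The workflow paragraphs of section 2 make IHC use follow from whether the pathologist sees tumour on the H&E slide. Section 3.4 says that in both arms the pathologist decides on IHC.

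For the analysis, protocol section 6.1 plans that "a simple Chi-squared test will be used to test for differences in the proportion of IHC-use in both arms", with adjustment for patient and tumour characteristics if they differ. Section 6.2 compares reading time by t-test or Mann-Whitney test. The SAP (Primary endpoint analysis) restricts the comparison to specimens with detected metastases. It uses a log-binomial model with 1,000 bootstrap replicates and gives no resampling unit. On tumour characteristics that affect visibility it says: "Two of these potential confounding factors were identified". These are metastasis size and histologic subtype.

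Nowhere do the documents give the number of readers, the length of a duty turn, the roster cycle, or a check of readers by arm.

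**The concern.** The reader is a direct cause of the outcome. A pathologist who finds more small metastases on H&E orders less IHC, with or without AI, and reading time is also a property of the reader. The only protection against reader differences is the sentence claiming balance. No test, model, interval or sample-size term allows for readers or two-week periods.

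A strict two-on, two-off calendar and a regular duty roster are both periodic. If their periods line up, the same pathologists always read with AI and the others always read without it. The comparison between arms is then also a comparison between groups of readers, and nothing in the plan would show this.

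**Working it through.** **Inputs from the documents.** From protocol section 3.4: 83 specimens in three months, 68 with IHC, 24 with metastases. All 8 macro-metastases were found without IHC, as were 2 of 8 micro-metastases and 0 of 8 isolated-tumour-cell (ITC) cases. Planned size is 90 per arm over 7 to 8 months. Derived: 83 in about 13.1 weeks is 12.6 specimens per two weeks, of which 12.6 x 24/83 = 3.65 are positive. 180/12.6 gives about 14 blocks, and 7 to 8 months gives about 15-17. Positives per arm: 90 x 24/83 = 26. The documents give no intraclass correlation (ICC), so all ICC values below are assumptions.

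**1. The plan's own figure.** With p1 = 68/83, p2 = 54/83 and mean 61/83, n = [1.645 x sqrt(2 x 0.735 x 0.265) + 0.842 x sqrt(0.148 + 0.227)]^2 / 0.1687^2 = 83.61 per arm. This matches the protocol and treats specimens as independent. Power at 90 per arm is 82.5%.

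**2. Roster against calendar.** I enumerated 28 weeks with one reader on duty at a time, turns starting in step with the AI switch, and no leave or swaps. Net imbalance is the sum over readers of |AI weeks - control weeks|, divided by 28.

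| Readers | One-week turns | Two-week turns |
|---|---|---|
| 2 | 0% (each 7/7) | 100% (14/0 and 0/14) |
| 3 | 7% | 14% |
| 4 | 100% (7/0, 7/0, 0/7, 0/7) | 100% |
| 5 | 21% | 29% |
| 6 | 14% | 100% |
| 7 | 0% | 0% |
| 8 | 100% | 100% |

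Readers are locked to an arm exactly where the full rotation (readers x turn length) is a multiple of 4 weeks. For two-week turns this also needs the turns to start when AI switches: offset by one week, each turn has one week in each arm.

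**3. Variance inflation from the blocks.** Design effect DE = 1 + (m - 1) x ICC; two-sided error = 2 x [1 - Phi(1.96/sqrt(DE))].

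- Metastasis-only, m = 3.65: ICC 0.02 gives DE 1.05 and 5.6%; ICC 0.05 gives DE 1.13 and 6.6%. Beta-binomial simulation (14 blocks of 4) gives 5.4% and 6.3%.
- All specimens, m = 12.6: ICC 0.01 gives DE 1.12 and 6.4%; ICC 0.02 gives DE 1.23 and 7.7%. Simulation (14 blocks of 13) gives 6.3% and 7.6%. Power at 90 per arm falls to 78.7% and 75.1%.
- On the one-sided 5% scale used for the sample size, the all-specimen errors are 6.0% and 6.9%.

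**4. How large the reader ICC can be.** If readers differ only in finding the 16 micro-metastasis and ITC cases (mean detection 2/16 = 0.125), the largest all-specimen ICC is (16/83)^2 x 0.125 x 0.875 / (0.819 x 0.181) = 0.027. If only the 10 H&E-detected cases skip IHC, it is 0.038. An ICC of 0.02 needs a between-reader SD of sqrt(0.02 x 0.148)/(16/83) = 28 percentage points. An SD of 10 points gives an ICC of 0.0025. Among positives the same 10 points is (16/24)^2 x 0.01 / (0.583 x 0.417) = 0.018, so ICC 0.02-0.05 is a plausible range there.

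**5. Bias if readers are locked to arms.** Suppose, as an illustration, that the AI-arm readers would find 10 percentage points more of the micro-metastasis and ITC cases without any AI. IHC use then differs by 0.10 x 16/24 = 6.7 points among positives (a spurious relative risk of 0.775/0.875 = 0.89) and by 0.10 x 16/83 = 1.9 points among all specimens. The planned difference is 14/83 = 16.9 points among all specimens.

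**The case against.** The roster is unknown. On one natural reading of the protocol, a schedule that repeats every one or two weeks, each two-week period holds a full cycle and the balance statement is correct. Locking needs a particular rotation length, one reader at a time and no swaps. A reader might infer that the usual rosters confound reader with arm, or that this happened here. The documents support neither. This stands, and it limits the point to balance not being guaranteed.

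A reader might also infer that p-values are generally too optimistic, or carry the arithmetic to an all-specimen ICC of 0.05 (12% two-sided error, about 65% power). That ICC is above the 0.027-0.038 ceiling in step 4, provided the IHC rule is followed and readers differ only in finding small metastases. Period effects of other kinds are not bounded this way, but the protocol reports no earlier case-mix variation or time trends. If readers are balanced across arms, ignoring them is slightly conservative: simulation with six balanced readers gives 4.8% at ICC 0.02 and 4.3-4.4% at ICC 0.05.

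Lastly, adjustment fails where the problem is worst. If each reader works in only one arm, a reader term cannot separate reader from AI, and block-robust errors do not remove bias. This also stands, and it is why the calendar matters more than the model.

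**Conclusion.** The claim of ensured balance is not supported by the premise given for it. The same premise allows full balance and full confounding, depending on a rotation length that is not reported. The gap matters because the reader drives both IHC use and reading time, and no planned analysis would detect or allow for a reader difference.

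The main risk is bias under a locked roster, not the block-level variance. On the SAP's metastasis-only denominator, error stays close to nominal; on the all-specimen test the inflation is real but limited. These sizes rest on assumed ICCs, equal block sizes and about 14 blocks. The bias example rests on an assumed 10-point reader difference and is well below the planned effect, but it would count for more if the true AI effect were smaller than planned. This is a worthwhile and inexpensive correction, not a demonstration that the comparison is invalid.

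**What to change.** 1. **Calendar (essential).** Before allocation starts, state the number of readers and the roster cycle, and set the AI calendar so that each reader works in both arms. Alternatively, randomise the order within each consecutive pair of two-week periods. Replace the word *ensures* by that check. Two-week switching stays, so the protocol's objection to case-by-case switching is respected. A reader with only one turn still cannot appear in both arms.
2. **Table.** Report specimens, and metastasis-positive specimens, by reader and arm.
3. **Analysis.** Add reader to the primary and reading-time analyses, at least as a prespecified sensitivity analysis. With about 26 positives per arm, use a random effect or stratification rather than many fixed terms. Resample two-week blocks in the bootstrap.
4. **Limit.** State in advance that if readers prove to be nested in arm, adjustment cannot separate the reader effect from the AI effect, and the conclusion must say so.

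The SAP is written in the past tense. Where allocation is already complete, items 2 to 4 remain possible if reader and date were recorded, which the documents do not state. The cost is a calendar check and some code, somewhat wider intervals, and block-based inference from only about 14-17 blocks.

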### **Current clinical workflow**

Sentinel lymph node specimens are first assessed digitally by the pathologist, on the regular hematoxylin and eosin (H&E) staining. If the pathologist detects metastases, no additional IHC stainings will be performed. If no metastases are detected on the H&E slide by the pathologist, additional IHC stainings are performed in all cases, to ensure no metastases are being missed.

### **Proposed clinical workflow (see figure below)**

Pathologists in the control arm will perform assessment according to the current clinical workflow. Pathologists in the AI-intervention arm will assess the HE-specimens digitally after the algorithm has assessed these. The output of the algorithm will be available to the pathologist when they assess the H&E specimen. Like in the control arm, if no metastases or tumors are detected on the H&E slide with AI assistance, additional IHC stainings are being performed in all cases, to ensure no metastases or tumors are being missed.

Therefore, the only direct benefit from the algorithm, in this first clinical introduction of AI tumor detection, will be the confirmation of metastases or tumor by the AI-assisted pathologist, in cases for which the non-AI-assisted pathologist would need IHC.

In a second phase, as the reference standard (IHC) will have been determined in all cases for which the AI-assisted pathologist concluded that no tumor or metastases were morphologically visible, we will be analyzing the safety of omitting IHC in these cases.

[figure not shown]

### 3. STUDY POPULATION

#### 3.1 Population (base)

All SN-specimens of women with a biopsy confirmed diagnosis of breast cancer being assessed in the UMC Utrecht, starting from (envisioned) April 2022 will be included and to have their lymph node specimen to be assessed by a pathologist with or without AI assistance.

#### 3.2 Inclusion criteria

In order to be eligible to participate in this study, a subject must meet all of the following criteria:

- Females any age
- Breast cancer as primary malignancy
- SN-specimen assessed at the UMC Utrecht

#### 3.3 Exclusion criteria

- Revisions from other clinics

#### 3.4 Sample size calculation

All SN-specimens assessed within the UMC Utrecht for three consecutive months (August 1st – November 1st 2021) were analyzed. In total, 83 SN-specimens were assessed, for which in 68 cases (81.9%) IHC was performed.

In 24/83 SN-specimens metastases were detected (8 macro-metastases, 8 micro-metastases, and 8 x isolated tumor cells).

- o All 8 macro-metastases were detected without IHC
- o 2/8 micro-metastases were detected without IHC
- o None of the 8 cases with isolated tumor cells were detected without IHC

We presume that the AI-algorithm will detect all metastases for which currently IHC is used. This means that for 14 metastases (6 micro-metastases + 8 ITC) no IHC will be used in the intervention group, whereas in the control group, IHC would be used. This leads to the following proportions per arm:

- $P1 = 68/83 = 0.819$
- $P2 = (68-14)/83 = 0.651$

A one-sided test was used, as we are only interested in a one-sided outcome, i.e. less IHC being performed in the AI-assisted arm. In addition, it is not likely that more IHC will be performed in the AI-assisted arm, as in both arms pathologists make the call whether to perform IHC. So even if the AI-algorithm would not recognize any metastases, the

pathologist would still look at the HE-slide and check whether there are no metastases (morphologically), which is exactly what the pathologists in the other arm are doing.

Calculations were performed in R by using the `power.prop.test` command (see below).

```
> power.prop.test(n=NULL, p1=0.819277108, p2=0.650602409, sig.level=0.05, power=0.8, alternative = "one.sided")

Two-sample comparison of proportions power calculation

      n = 83.61041
     p1 = 0.8192771
     p2 = 0.6506024
sig.level = 0.05
  power = 0.8
alternative = one.sided

NOTE: n is number in "each" group
```

We decided to be conservative and include 90 SN-specimens (i.e. from 90 patients) per arm. This will take approximately 7 to 8 months.

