### **7.2 Recruitment and consent**

Informed consent is not required for the following reasons:

1. Standard care, i.e. assessment by a pathologist and IHC when no tumor cells are detected, is performed in all cases. Hence, there is no chance of an inferior diagnosis (missed tumor cells). Also, patients (more specifically their tissue specimens) are not subjected to any actions, nor are rules of conduct imposed on them. Therefore, overall patients just receive standard care and are at no risk. One could also think of it like performing an extra staining in routine diagnostics, for which informed consent is never required.
2. Secondly, all data will be anonymous to the researchers.

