### Sample size calculations

Sample size calculations were based on a retrospective analysis of 83 consecutive SN-specimens from a period of three months in the UMC Utrecht. We assumed that the AI-assisted pathologist would detect all metastases without IHC for which currently IHC is needed, which are mainly micro-metastases and ITC (~15%). Of the 83 cases, IHC was used in a total of 68 cases (0.819), mainly consisting of negative cases and 14 cases of ITC and micro-metastases. We assumed that these 14 cases would be detected by the algorithm, without the need for IHC. This resulted in a presumed proportion of IHC-use in the intervention arm of 0.650 (54/83). This sample size calculation is thus built on two assumptions, being a presumed similar overall distribution of negative cases and cases of ITC, micro- and macro metastases during the trial, and a presumed proportion of IHC-use in the intervention arm based on assumptions of the accuracy of the algorithm. Therefore, the sample size calculation is in theory indirect. However, it was deemed the best way calculate clinically applicable sample sizes for this trial.

We used a one-sided significance level of 5%, as it was deemed impossible to use more IHC

after AI-assistance, and a power of 80%, resulting in a sample size of 166 SNs (83 per arm). As there are uncertainties on the assumption of the amount of metastases that the AI-assisted pathologist would detect without IHC, we decided to include 180 SNs (90 per arm) to be on the safe side.

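### The pilot count of 68 stained specimens does not fit the rule of IHC in every H&E-negative specimen: at least 5 of 83 are unaccounted for

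*Combined protocol and SAP*

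**What the plan says.** Protocol section 3.4 gives the pilot totals: "In total, 83 SN-specimens were assessed, for which in 68 cases (81.9%) IHC was performed". It gives the positives as follows: "In 24/83 SN-specimens metastases were detected (8 macro-metastases, 8 micro-metastases, and 8 x isolated tumor cells". It then breaks down the 24 positives: "All 8 macro-metastases were detected without IHC"; "2/8 micro-metastases were detected without IHC"; "None of the 8 cases with isolated tumor cells were detected without IHC". From these it takes P1 = 68/83 and P2 = (68 − 14)/83, obtains 83.61 per arm (one-sided 5%, 80% power) and plans 90 per arm.

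The SAP, under Sample size calculations, repeats the count: "IHC was used in a total of 68 cases (0.819), mainly consisting of negative cases and 14 cases of ITC and micro-metastases".

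The staining rule is in protocol section 2, Current clinical workflow: "If no metastases are detected on the H&E slide by the pathologist, additional IHC stainings are performed in all cases". The Proposed clinical workflow carries the same rule into the AI arm. Section 7.2 relies on it to justify the absence of informed consent: "Standard care, i.e. assessment by a pathologist and IHC when no tumor cells are detected, is performed in all cases".

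Two other places are worded more loosely. Section 3.4 says that pathologists in both arms decide whether to stain, and section 4.4 ties IHC to cases of doubt.

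**The concern.** The pilot total, the breakdown of positives and the staining rule cannot all be right as written. Two things depend on them.

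First, 68 is the numerator of P1 and the starting point for P2, so a miscount would pass straight into the sample size.

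Second, staining of all negatives is the safety standard named in the primary objective. It also supplies the reference standard for the planned second-phase analysis of omitting IHC, and it supports the consent argument. An H&E-negative specimen without IHC has no reference result. If such specimens also occur in the trial, the plan has no rule for them: section 6 expects no missing data, and the SPIRIT-AI checklist marks the item on analysis population and missing data as not applicable.

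**Working it through.** **Inputs** (protocol section 3.4): 83 specimens; 68 with IHC; 24 positive; found without IHC: 8 macro, 2 micro, 0 ITC; one-sided alpha 0.05; power 0.80.

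**1. The plan's own figure.** With p̄ = (P1 + P2)/2 and d = P1 − P2,

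n = [1.645·√(2p̄(1 − p̄)) + 0.842·√(P1(1 − P1) + P2(1 − P2))]² / d².

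For P1 = 68/83 = 0.819, P2 = 54/83 = 0.651 and d = 14/83 = 0.169, n = 83.61 per arm. This matches the printed R output. Power at 90 per arm is 82.5%.

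**2. The counts.**
- Found on H&E: 8 + 2 + 0 = 10.
- H&E-negative: 83 − 10 = 73, made up of 83 − 24 = 59 negatives and 24 − 10 = 14 positives that needed IHC.
- Stained: 68, of which 14 were positive, leaving 68 − 14 = 54 stained negatives out of 59.
- Gap: 73 − 68 = 5. Equivalently, 83 − 68 = 15 specimens had no IHC but only 10 were found on H&E.

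Five is a minimum: if any of the 10 H&E-detected specimens was also stained, fewer than 54 negatives were.

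**3. Three ways to close the gap** (same formula and alpha):

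| Reading | P1 | P2 | n per arm | Power at 90 |
|---|---|---|---|---|
| (a) 68 is a miscount; 73 were stained | 73/83 = 0.880 | 59/83 = 0.711 | 69.7, so 70 | 88.2% |
| (b) 68 is right; 5 negatives were not stained | 68/83 = 0.819 | 54/83 = 0.651 | 83.6 | 82.5% |
| (c) 68 and the rule are right; 15 were found on H&E | 68/83 = 0.819 | 59/83 = 0.711 | 188 | 52.8% |

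Reading (c) assumes that the 24 positives stand, so that only 24 − 15 = 9 could be spared IHC. Under (b) the unstained share of negatives is 5/59 = 8.5%.

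**4. What unverified specimens do to accuracy, under (b).** Counting the five as true negatives gives an H&E sensitivity of 10/24 = 41.7% and an NPV of 59/73 = 80.8%. If all five held metastases, these would be 10/29 = 34.5% and 54/73 = 74.0%. Leaving the five out gives an NPV of 54/68 = 79.4%. Calling unstained specimens true negatives can therefore only raise these measures or leave them unchanged.

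**The case against.** The best defence is that the gap does little harm to the trial, and much of that stands.

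- **Sample size.** The calculation reproduces. Under (a) and (b), 90 per arm is enough for the planned one-sided test. Only (c) leaves the trial underpowered, and it contradicts the type-by-type counts in section 3.4 and the 14 cases repeated in the SAP. The SAP is in the past tense and the checklist says results have been presented, so rerunning n now corrects the record, not the recruitment.
- **Primary endpoint.** Section 5.1.1 and the SAP's primary analysis are confined to detected metastases. A specimen reported negative without IHC is not in that denominator. The pilot control proportion is 14/24 whether 68 or 73 were stained. Only the all-specimen comparison in sections 3.4 and 6.1 is exposed.
- **False savings.** A reader might set 5/83 × 90 = 5.4 unstained negatives per arm against the planned effect of 14/83 × 90 = 15 specimens. That compares a level within one arm with a difference between arms. If non-staining is equal, the difference stays at 14/83. Bias needs non-staining to differ by arm. The absence of blinding makes that possible, but nothing in the documents shows it.
- **Missed metastases.** A reader might apply the pilot yield among stained specimens, 14/68 = 20.6%, to those 5.4 and infer about 1.1 undetected metastases per arm. Why the five went unstained is unknown, so their risk is unknown too. The count could be anything from 0 to 5.4.
- **Pilot versus trial.** The pilot is a retrospective 2021 series, and the plan does not say that the trial's eligibility criteria were applied to it. It cannot show that the rule failed during the trial.

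None of this explains the five specimens.

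**Conclusion.** The inconsistency is certain, because it follows by subtraction from the plan's own counts. At least one of three things is wrong as written: the 68, the H&E-detected counts, or the statement that all H&E-negatives are stained. The documents do not allow a choice.

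It would be tempting to conclude that P1, P2 and n are wrong. That follows only if a count is wrong. If 68 is what was observed, all three stand and the fault lies in the workflow statement, for 8.5% of pilot negatives on the assumption that none of the 10 H&E-detected specimens was stained. It would be equally tempting to put 73 in place of 68, but 73 is what the rule implies, whereas 68 is reported in both the protocol and the SAP.

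Any inflation of sensitivity and NPV in the trial depends on unstained negatives recurring there and being counted as true negatives.

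**What to change.** 1. Trace the 5 (or more) specimens in the pilot records, without presuming that 73 is the right count.
2. Correct whichever proves wrong: the counts together with P1, P2 and n (section 3.4 and the SAP's Sample size calculations), or the statements on staining (Current and Proposed clinical workflow, section 7.2). Reconcile section 3.4's remark on pathologists' discretion with those statements.
3. Tabulate H&E-negative specimens without IHC by arm.
4. In sensitivity and NPV, treat these specimens as unverified, not as true negatives.
5. In the all-specimen comparison of IHC use (section 6.1), do not credit them as avoided IHC, for example in a sensitivity analysis. The metastasis-only primary endpoint needs no such recoding.

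The cost is one check of the pilot records, one rerun of the power calculation if a count changes, and a few sentences and one small table in the SAP.
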